### CBSST effectiveness mediators (Aim 2)

The primary mediation analysis will be based on the recommendations of Kraemer et al. [53] using a similar linear mixed-models approach. Two conditions must be met for mediation of the treatment effect: 1) correlation between the mediator and treatment (ACT versus ACT + CBSST group effect on MASC or DPAS), and 2) relationship between the mediator and outcome (MASC or DPAS main effect or group × MASC or group × DPAS interaction on ILSS). A statistically significant effect of treatment group on the outcome is not required, according to Kraemer et al. [54], although this will be tested in Aim 1. First, we will test the effect of treatment group and the group × time interaction on the mediator (MASC or DPAS score across all available assessments). Here we are looking for a statistically significant treatment group × y time interaction. Second, we will test the effects of MASC or DPAS change (slope across available assessments) and the MASC or DPAS change × group interaction on the outcome (ILSS across all available assessments) in the model that includes group and time. Here we are looking for a statistically significant MASC or DPAS change main effect or significant MASC or DPAS change × group interactions.

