Consistent with a “Hybrid Type 1” design, the primary aims of the proposed project are to evaluate whether the CBSST program, when provided by ACT staff in the context of usual ACT services, improves functioning in schizophrenia more than ACT alone. A secondary aim is to examine potential mechanisms of change in functioning in CBSST, which could have implications for refining the CBSST treatment program. Specifically, CBSST attempts to teach social skills and modify defeatist performance beliefs (e.g., “It’s not worth the effort,” “It won’t be fun”) that can interfere with community functioning [13], so we will examine whether improvement in social skill competence and reduction in defeatist performance beliefs mediate improvements in psychosocial functioning in CBSST. Finally, an exploratory aim is to use mixed qualitative-quantitative methods (i.e., CM, qualitative interviews, staff and supervisor surveys) to identify barriers to, and facilitators of, successful implementation of CBSST across ACT teams. We will examine the perspectives of multiple stakeholders in the service system, including administrators and clinicians in provider organizations, and consumers. We expect that there will be both congruence and differences in perceptions of barriers/facilitators across stakeholder groups and that policy, funding, organizational process, and provider and consumer preferences will be important in implementation success and generalizability.

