#### Aim 2-effectiveness mediators

To determine whether improvement in social competence and reduction in defeatist beliefs mediate changes in psychosocial functioning in CBSST in consumers with schizophrenia.

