#### Mediator measures

The Maryland Assessment of Social Competence (MASC) will be used in the mediator analyses. The MASC is a structured behavioral role-play assessment that measures the ability to resolve interpersonal problems through conversation [44, 45]. The MASC takes about 15–20 minutes to administer and consists of three 3-minute role-play communication scenarios (1 conversation initiation and 2 assertion), during which the consumer interacts with a live confederate who plays a role (e.g., boss) in a problem-oriented situation (e.g., asking for a work shift change). The measure has three parallel sets of scenarios for multiple administrations. Videotaped role plays are rated by blinded raters on dimensions of verbal content, nonverbal communication behavior, and overall effectiveness, which will be the primary MASC variable. The Defeatist Performance Attitude Scale (DPAS) is a 15-item self-report subscale of the commonly-used 40-item Dysfunctional Attitude Scale (DAS) [46, 47] that was derived from factor analysis. The DPAS indexes generalizes defeatist beliefs about one’s ability to perform tasks and effectiveness of social behaviors (e.g. “If you cannot do something well, there is little point in doing it at all,” “If I fail at my work, then I am a failure as a person”). Providers will document the completion of CBSST sessions, including whether homework was completed and the level of consumer participation in CBSST sessions, which will be explored as potential mediators of treatment outcome.

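### Step 2 of the mediation analysis tests average ILSS level, not change in ILSS, over the same visits as the mediator slope, so it does not answer Aim 2 and cannot show direction

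*Protocol article*

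**What the plan says.** The Aim 2 statement sets the target as change: "To determine whether improvement in social competence and reduction in defeatist beliefs mediate changes in psychosocial functioning in CBSST". The Background repeats it: "we will examine whether improvement in social skill competence and reduction in defeatist performance beliefs mediate improvements in psychosocial functioning in CBSST".

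The section CBSST effectiveness mediators (Aim 2) then fixes the test. "Two conditions must be met for mediation of the treatment effect: 1) correlation between the mediator and treatment"; the second condition is a mediator–outcome relationship. Time order between mediator and outcome is not a condition. Step 1 looks for a group × time effect on the mediator. Step 2 reads "Second, we will test the effects of MASC or DPAS change (slope across available assessments"), together with the interaction of that slope with group, "on the outcome (ILSS across all available assessments) in the model that includes group and time". The deciding rule is: "Here we are looking for a statistically significant MASC or DPAS change main effect or significant MASC or DPAS change × group interactions".

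No mediator-change × time term, lag or early-change window is given. Baseline ILSS is not among the example covariates under Analyses.

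**The concern.** Step 1 is about change over time and step 2 is not. A person's mediator slope is one number per person. Entered beside group and time, its main effect says whether people with steeper slopes have higher ILSS on average over all visits. Its interaction with group says whether that differs by arm. Neither says whether their ILSS rose more.

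The slope also uses visits up to the end of follow-up, while the outcome includes ILSS at earlier visits and before treatment. Randomization puts treatment before the mediator. It does not put the mediator before ILSS.

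Aim 2 is the stated secondary aim, and the Background says its result could guide refinement of the CBSST programme. A result driven by baseline level, or by functioning changing beliefs, would misdirect that work.

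**Working it through.** The document gives no figure for mediation power or error, so there is none to reproduce.

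**What the named term estimates.** Code the five visits t = 0, 1, 2, 3, 4 (mean 2). Write ILSS for a person as I + S·t + error, and the mediator slope as s. With complete data and a random intercept, the coefficient of a person-level predictor equals that from regressing each person's mean ILSS on s and group. Mean ILSS is I + 2S + error, so the main effect tests, within group,

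C = cov(I, s) + 2·cov(S, s).

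Aim 2 concerns cov(S, s) only. A change × time term tests that alone.

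**Illustration.** From the protocol: 70 per group, five visits, two-sided 0.05. Assumed, not in the document: SD of I 0.7, SD of true slope 0.15 per visit, residual SD 0.6, path from mediator slope to ILSS slope 0.8, treatment effect on the driving variable 0.6 over the study, and correlation r between baseline ILSS and true mediator slope from −0.5 to +0.3. Then 2·cov(S, s) = 2 × 0.8 × 0.15² = 0.036 under true mediation and 0 with no link between the changes; cov(I, s) = r × 0.7 × 0.15 = 0.105r. Rejection rates are from 3,000 simulated trials each.

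| r | C, true mediation (0.036 + 0.105r) | Planned main effect rejects | C, no link (0.105r) | Planned main effect rejects | Change × time rejects: mediation / no link |
|---|---|---|---|---|---|
| −0.5 | −0.0165 | 0.22 | −0.0525 | 0.90 | 0.97 / 0.04 |
| −0.3 | 0.0045 | 0.06 | −0.0315 | 0.47 | 0.97 / 0.05 |
| 0 | 0.036 | 0.61 | 0 | 0.05 | 0.96 / 0.055 |
| +0.3 | 0.0675 | 0.98 | 0.0315 | 0.47 | 0.96 / 0.05 |

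The planned test follows C. Under true mediation C vanishes at r = −0.036/0.105 = −0.34 and is negative beyond that. With no link, it still rejects whenever r is not zero.

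**Sensitivity.** Varying the SD of I over 0.4–1.0 and of the slope over 0.10–0.20, the planned main effect rejects under true mediation in 0.12–1.00 of trials at r = 0 and 0.05–0.86 at r = −0.3. Change × time rejects in 0.52–1.00. The size of any loss is therefore not determined by what the document gives.

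**Direction.** If ILSS change drives mediator change with the same path, cov(S, s) is again 0.8 × 0.15² = 0.018. At r = 0 the planned test rejects in 0.59 of trials, against 0.61 for true mediation. Change × time rejects in 0.96 either way, so it does not settle direction. When one variable moves early and the other follows, the planned test at r = 0 rejects in 0.27 when the mediator leads and 0.84 when ILSS leads: ILSS that moves early lifts its own average over more visits.

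**Either-or rule.** Two roughly independent tests at 0.05 give 1 − 0.95² = 0.0975; simulation with no link and r = 0 gives 0.099. Step 1 must also be met. If it succeeds with probability p, independently, the joint rate is about p × 0.0975.

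**The case against.** An article compresses, and the full analysis plan may add terms. That would be an answer if the article were silent. It names the predictor, the outcome, the terms and the rule for success, so a plan using change × time would have to depart from it.

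The strongest objection concerns size. A reader might infer that a null result is likely even when mediation is real. The document does not support that: it gives no variances for MASC, DPAS or ILSS slopes, and the planned test ranges from almost no power to almost full power over plausible choices. This objection stands.

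A reader might also take 10% as the error rate for declaring mediation. It is the step 2 rate only. Both conditions are required, so the joint rate is at most about that, and much lower if treatment does not move the mediator.

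A third inference is that session completion, homework and participation, "which will be explored as potential mediators of treatment outcome" under Mediator measures, meet the first condition by definition because they exist only in the CBSST arm. The two-condition test names only MASC and DPAS, and nothing puts these exploratory variables through it.

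Finally, the obvious remedy has its own flaw: regressing late ILSS on early mediator change, adjusted for baseline mediator, baseline ILSS and group. When the baseline mediator is measured with error, stable level passes as change. With correlated stable levels and no effect of change, simulations under assumed variances rejected in 13%–43% of trials, and in 7%–22% with intermediate ILSS added, against about 5% for change × time.

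**Conclusion.** The point holds. Step 2 tests association with average ILSS level, while Aim 2 is about change. The test can miss true mediation of change and can be positive through baseline ILSS alone. It cannot separate mediator-led change from reverse causation. These conclusions follow from the stated terms and need no numerical assumption.

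The one size that can be stated is the step 2 error rate, about 10% instead of 5%, taking the two tests as roughly independent and baseline ILSS as unrelated to mediator change. The simulated rates show how the test can fail, not how often it will. The test is unreliable for this aim, not powerless. Only the secondary aim is affected; effectiveness rests on ILSS under Aim 1.

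**What to change.** In step 2, keep the mediator-change main effect and its interaction with group as lower-order terms. Make the deciding test the effect of mediator change × time on ILSS (equivalently, mediator slope against ILSS slope, with group in the model). Use one joint test of change × time and change × group × time at 0.05 in place of the either-or rule.

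Add a time-ordered analysis in which earlier mediator change predicts later ILSS change given earlier ILSS. Specify it so that error in the baseline mediator does not let stable level pass as change, for example with a latent stable level per person. If this is not done, state that direction cannot be concluded.

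Cost: a change of wording and somewhat more analysis, with every variable already collected. The time-ordered test will usually have less power: where both variables change steadily together, a simple version rejected in 0.11–0.85 of simulated trials against 0.52–1.00 for change × time, over the assumed variances above.

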### Statistical power calculation

The methods described by Diggle et al. [54] and Hedeker et al. [55] were used to calculate power, resulting in a sample size of *N* = 176. We assumed an autoregressive covariance structure, with conservative correlation between sequential assessments set at 0.45 and up to 4 covariates in the model. We powered our primary aim (Aim 1) for our primary outcome measure (ILSS) to detect a small to medium group × y time interaction effect. For the 2 (ACT + CBSST versus ACT alone) by 5 (assessment times) mixed-model analysis evaluating the treatment group effect over the course of the entire study, a sample size of 70 per group (20 % dropout) and *α* = 0.05 2-tailed, we would have minimum power of 0.85 to detect a small to medium (0.35) group × y time interaction effect.

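### The 0.85 power is attached to a 0.35 group × time interaction that is never defined and that the primary model does not name; an ordinary interaction test of 0.35 SD has power of 0.19 to 0.51

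*Protocol article*

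**What the plan says.** The section Statistical power calculation fixes nearly every input. On covariance it says "We assumed an autoregressive covariance structure", with "conservative correlation between sequential assessments set at 0.45". The analysed number is "a sample size of 70 per group (20 % dropout" allowed for), which leads to N = 176. On error rates it says "0.05 2-tailed, we would have minimum power of 0.85". The claim is that "we would have minimum power of 0.85 to detect a small to medium (0.35) group" × time interaction, and the same section names that interaction as the basis for powering Aim 1. Yet the sentence that gives the power describes the analysis as a "mixed-model analysis evaluating the treatment group effect over the course of the entire study".

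The section CBSST effectiveness analyses (Aim 1) lists a random intercept, a fixed effect for the five assessment points, and treatment group as predictors of the ILSS. It names no group × time term. The section CBSST effectiveness mediators (Aim 2) does name that term, for the mediators. The section Analyses says that effectiveness will be judged on the ILSS alone.

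**The concern.** The power section attaches 0.85 to an interaction, while the primary model, as written, tests a group effect. These contrasts have very different precision in a five-visit trial with serial correlation 0.45, so one effect size cannot carry the same power for both. The number 0.35 also has no stated scale or time. It could be a difference at 18 months, a difference averaged over follow-up, or something else.

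What is at stake is how a null result would be read. If the interaction is tested and is not significant, the stated power invites the conclusion that a small-to-medium effect has been ruled out with fair confidence. Whether that inference is sound depends on a definition that the protocol does not give.

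**Working it through.** **Inputs from the protocol.** n = 70 per group; two-sided alpha 0.05; five equally spaced assessments (baseline plus four, every 18 weeks); autoregressive correlation ρ = 0.45; effect 0.35.

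**Assumptions not in the protocol.** AR(1) form, SD = 1 at every visit, no variance reduction from covariates, normal approximation.

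**Sample size.** 70 / 0.8 = 87.5, so 88 per group and 176 in total. This agrees with the protocol.

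**Method.** For a contrast c over visits, SE = √(2·c′Vc / 70) and power ≈ Φ(effect/SE − 1.96). V has entries ρ^|i−j|.

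**Readings that recover about 0.85**

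1. Mean of the four follow-ups, difference 0.35. c′Vc = [4 + 2(3ρ + 2ρ² + ρ³)]/16 = 0.4808. SE = √(2 × 0.4808/70) = 0.1172; z = 2.99; power 0.848. This is a group main effect.
2. Linear interaction from 0 to 0.70 at the last visit, which averages 0.35 over the five visits. The per-subject variance of the GLS slope is 0.1172, so SE = 0.0579. Slope 0.70/4 = 0.175; power 0.856 (0.844 with an OLS slope). Solving for exactly 0.85: 4 × (1.960 + 1.036) × 0.0579 = 0.69 SD.
3. Follow-up mean adjusted for baseline, constant 0.35. The covariance of the follow-up mean with baseline is (ρ + ρ² + ρ³ + ρ⁴)/4 = 0.1962, so the variance is 0.4808 − 0.1962² = 0.4423; SE = 0.1124; power 0.876.
4. Mixed model with arms constrained equal at baseline and a constant 0.35 afterwards: SE = 0.1093; power 0.893.

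**Unconstrained interaction tests with 0.35 SD as the size of the effect**

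| Test | Calculation | Power |
|---|---|---|
| Linear, reaching 0.35 at the last visit, GLS | 0.0875/0.0579 = 1.51 | 0.327 |
| Same, OLS slope | variance 0.1214, SE 0.0589, z = 1.49 | 0.318 |
| Baseline-to-last-visit change | variance 2(1 − ρ⁴) = 1.918 | 0.321 |
| Follow-up mean minus baseline, constant 0.35 | variance 0.4808 + 1 − 2(0.1962) = 1.088, SE 0.1763, z = 1.98 | 0.510 |
| 4-df interaction, linear to 0.35 | noncentrality 2.29 | 0.19 |
| 4-df interaction, constant 0.35 | noncentrality 4.57 | 0.36 |

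**Sensitivity of the linear-to-0.35 case.** 88 per group with no dropout: 0.396. Gradual dropout from 88 to 70: 0.361. Compound symmetry at 0.45 in place of AR(1): 0.598. Slope constrained to equal arms at baseline: 0.607. None reaches 0.85.

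**Dependence on ρ** (70 per group)

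| ρ | Linear interaction to 0.35 | Unadjusted follow-up mean, 0.35 | Baseline-adjusted follow-up mean, 0.35 |
|---|---|---|---|
| 0.45 | 0.33 | 0.85 | 0.88 |
| 0.6 | 0.35 | 0.77 | 0.84 |
| 0.7 | 0.39 | 0.71 | 0.85 |
| 0.8 | 0.48 | 0.65 | 0.89 |

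**The case against.** The strongest reply is that the protocol never places 0.35 at the last visit and never says that the difference grows linearly. The power sentence speaks of an effect over the whole study, and the Aim 1 model contains a group term. Both point to a time-averaged difference, and that reading returns 0.848. Even an interaction recovers 0.85 if 0.35 is its average over the five visits, and a baseline-constrained model with a constant 0.35 gives 0.89. This reply stands as far as it goes. A reader might infer that the power claim is simply false and that the trial has one chance in three of detecting its target. The documents do not support that, because 0.33 needs an assumption about shape and timing that they do not make.

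The reply does not rescue the text. If 0.35 is a follow-up average, the label of interaction is wrong. If it is the average of a linear divergence, the last-visit difference is about 0.70 SD, twice the printed number, and this is nowhere said. With time as five categories, the 4-df test of that same divergence has power of only 0.67. A baseline constraint is not stated either.

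A reader might also infer that calling ρ = 0.45 conservative is an error. For the linear interaction that the section names it is fair: power is nearly flat at first and then rises with ρ. The word fails only if the power rests on the unadjusted follow-up mean, where power falls as ρ rises.

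A journal article may shorten its model description. Here, though, two sections of the same article attach the primary test to different terms, which is more than an omitted detail.

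**Conclusion.** The concern holds in this form: the stated 0.85 is tied to a group × time interaction of undefined size, and the primary model as described does not name that interaction. The figure is reproducible for a 0.35 SD group difference averaged over follow-up, or for an interaction reaching about 0.70 SD at the last visit. It is not reproducible for any unconstrained interaction test tried in which 0.35 SD is the last-visit or constant follow-up difference; those give 0.19 to 0.51. Depending on the reading, power for 0.35 therefore runs from 0.19 to about 0.89, so what a null result means is open.

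The results rest on AR(1), equal SDs over time, 70 complete cases per group and no gain from covariates. The sample size arithmetic is sound.

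**What to change.** Name one primary contrast, in the same words, in the power section and the Aim 1 analysis section. State what 0.35 measures, in which SD units and at which visit or visits. Then restate the power by one of two routes.

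- Make the baseline-adjusted mean difference over the four follow-ups primary, and state power of about 0.84 to 0.89 for a constant 0.35 SD over ρ from 0.45 to 0.8.
- Keep the group × time interaction as primary, add it to the Aim 1 model, and state power of about 0.33 for 0.35 SD at the last visit and 0.85 only for about 0.70 SD.

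The description of ρ as conservative can stay if the linear interaction is kept; it should go if the power rests on the unadjusted follow-up mean.

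The cost is text only. N stays at 176. Under the second route the stated power for 0.35 SD at the last visit becomes much less favourable.

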### Mixed-method implementation study design (Aim 3)

Empirical literature suggests that effective dissemination and implementation must take into account the complexity of the service system and multiple levels at which change must occur (i.e., system, organization, individual) in conjunction with the technology or intervention to be disseminated [56–58]. In order to enhance the likelihood of success of future implementations, it is important to determine barriers to, and facilitators of, dissemination and implementation of EBPs, such as CBSST, in real-world service settings such as ACT teams [57, 58]. We will conduct an assessment of such factors using CM methodology to guide data collection and analysis [24, 59, 60]. CM is a mixed qualitative-quantitative method particularly useful with diverse stakeholders that may hold different perspectives and experiences with services [59]. We have used CM to identify barriers to, and facilitators of, EBP implementation in a large youth mental health service system [61] and will apply it here.

There are 6 steps in CM: 1) Preparation – participants are identified, the focus is developed, and a schedule of focus group meetings is set, 2) Generation – stakeholders participate in focus groups and brainstorm statements reflecting possible factors that may facilitate or interfere with the implementation of CBSST in ACT teams, 3) Structuring – each participant sorts the statements into piles based on similarity and then rates each statement on importance and changeability (described below), 4) Representation – data are used to conduct multidimensional scaling wherein each statement is a point on a “Concept Map” with statements piled together by more people closer to each other and cluster analysis is then used to aggregate similar groups of statements into clusters (described below), 5) Interpretation –- the investigators work with stakeholders to reach a consensus for labels and interpretations of the different clusters, and 6) Utilization involves using the maps to help address the original focus, in this case, to develop an implementation intervention to facilitate subsequent CBSST implementation in ACT teams in other settings. Thus, we will use an established method with the appropriate stakeholders to identify barriers to, and facilitators of, implementation and sustainability of CBSST on ACT teams.

The CM steps described above will be used to collect and organize the CM data and illustrate emergent concepts based on study participants’ responses. Initial CM data collection will occur after 7 ACT teams are trained and have delivered CBSST for at least 6 months. Investigators will meet with members from six stakeholder groups: consumers, ACT team members, ACT team leaders, organization administrators, University of California, San Diego (UCSD) research team members, and county representatives. A total of 75–100 participants will complete CM study-related activities. We will explain that the goal is to identify barriers to, and facilitators of, CBSST implementation in ACT teams in public sector mental health settings. The experience of being involved in the implementation of CBSST on these ACT teams will serve as the focal experience. If upper management and policy stakeholders lack in-depth knowledge of the intervention and setting we will provide detailed descriptions and engage the group in discussion to illustrate the process of implementation and service delivery. Thus, collectively, stakeholder participants will be familiar with the intervention, training requirements, intervention duration and frequency, case-manager experience/education, perceived cost/benefit, training experience, and consumer experience with the intervention.

The group will develop a focus statement to guide group brainstorming. An example focus statement is: *“What are the factors that influenced the implementation and use of CBSST in ACT teams in this mental health system?”* Study investigators will then facilitate focus group sessions with each stakeholder group separately in order to promote candid responses and reduce desirability effects while brainstorming barriers to, and facilitators of, implementation and sustained use of CBSST in ACT teams [60]. It is likely that a large number of statements (e.g., 200) will be generated when aggregated across stakeholder groups. Our past experience has shown that by eliminating duplicate statements and combining similar statements, a large number of statements can be distilled into about 100 distinct statements [61]. After randomly renumbering statements to minimize priming effects, a member of the research team will meet individually with each of the original stakeholders and present the cards (one statement per card) and ask each stakeholder to sort similar statements into the same pile, yielding as many piles as he/she deems appropriate [62]. Finally, each participant will be asked to rate each statement on a 1 to 5 point scale on “Importance” (from 1 – “Not at all important” to 5 – “Extremely important”) and “Changeability” (from 1 – “Not at all changeable” to 5 – “Extremely changeable”). This may appear a daunting task, but we have successfully used such techniques with mental health consumers in the past.

Multidimensional scaling and hierarchical cluster analysis will then be used to generate a visual display of how statements are clustered across all participants [63]. The result will be a single “Concept Map” depicting which statements participants had frequently sorted together. Multiple study investigators will independently evaluate potential solutions (e.g., 12 clusters, 15 clusters) and agree on the final model based on a statistical “stress” value and interpretability [62, 63]. CM requires small sample sizes and having 4–6 participants for each stakeholder group will suffice for this work [24]. Finally, study participants will reconvene with the research team in order to define the meaning and a name for each of the final clusters.

